#### Potential Efficacy

In terms of *primary clinical measures*, *social functioning* was measured using the interviewer-administered Social and Occupational Functioning Assessment Scale that comprises a 100-point single item to assess social and occupational functioning [3] and the interviewer-administered Personal and Social Performance Scale that consists of a 100-point single item to assess functioning in four domains: socially useful activities (including work and study), personal and social relationships, self-care, and disturbing and aggressive behaviors [48]. In terms of *secondary clinical measures*, *global improvement and therapeutic response* was assessed using the clinician-administered Clinical Global Impression Scale that consists of two items to assess global improvement and severity of illness [49]. We also assessed *social support* using the self-reported Multidimensional Scale of Perceived Social Support that includes 12 items (eg, “I get the emotional help and support I need from my family) [50]; *self-esteem and perceived strengths* using the self-reported Self-Esteem Rating Scale that consists of 40 items (eg, “I feel that I am a very competent person”) [51], the self-reported Strengths Knowledge Scale that includes 8 items (eg, “I know what I do best”) [52], and the self-reported Strengths Use Scale that consists of 14 items (eg, “I am regularly able to do what I do best”) [52,53]; and *symptoms* using the following interviewer-administered assessments: the Scale for the Assessment of Positive Symptoms that consists of 34 items in four symptom domains (hallucinations, delusions, bizarre behavior, and positive formal thought disorder) [54]; the Scale for the Assessment of Negative Symptoms that includes 25 items in five symptom domains (affective flattening or blunting, alogia, avolition-apathy, anhedonia-asociality, and attention) [55]; the Brief Psychiatric Rating Scale that includes 24 items assessing psychiatric symptoms such as somatic concern, anxiety, depression, and suicidality [46]; and the Calgary Depression Scale that includes nine items assessing depressive symptoms such as depressed mood, hopelessness, and suicide [56].

#### Qualitative Measures

Qualitative data on the acceptability, safety, and impact of the intervention was mainly obtained at the 4 weeks follow-up through the *HoryzonsCa Meet-up and Focus Group* discussion meeting.

The research assistant took field notes on any additional comments from participants related to their experiences and perspectives of the intervention during the *HoryzonsCa Initial Interview and Orientation Meeting* (which occur at baseline) and the HoryzonsCa Exit Interview (which occur at the 8 weeks follow-up). Moreover, participants were asked open-ended questions at the end of the HC-AUSI-Q, which were conducted during the *HoryzonsCa Exit Interview*.

At the *HoryzonsCa Initial Interview and Orientation Meeting* (60 minutes), participants completed the baseline measures (as described in previous sections), received an introduction to the website including review of its Terms of Use, and were provided with password information to log into the website using a pseudonym when logged in. They were invited to complete 3 to 5 activities (eg, identifying strengths and values through a card sorting activity and writing a short post in the café) and had the opportunity to ask questions and make comments about the intervention platform. The research assistant took field notes on participants’ initial impressions and questions about the website, concerns raised by the participant, and any challenges observed in navigating the intervention platform.

The *HoryzonsCa Meet-Up and Focus Group* (120 minutes) occurred midway through the 8 weeks of follow-up. We invited all participants to this Meet-up and Focus Group Meeting, and aimed to have approximately 4 to 8 participants each session. The focus groups were facilitated by the project lead with the support of a research assistant. Before having a focused discussion on the platform, the facilitator (who does not have any clinical role or therapeutic relationship with the participants) welcomed participants, provided an overview of the meet-up objectives, and provided logistic information (eg, duration of group and scheduled breaks). After that, participants were invited to share their experiences and perspectives of the system, and feedback on factors that support or hinder its use. Specifically, the topics of the focus group were general impressions of the HoryzonsCa intervention platform (eg, likes and dislikes), how easy it is to use, how useful the intervention platform has been for well-being, how the intervention platform can be improved to better meet the needs of Canadian youth, and any other suggestions in implementing and evaluating HoryzonsCa. The interview guides for the focus groups were adapted from our phase 1 adaptation study protocol, which was informed by the eHealth Adaptation Framework [31]. The facilitator encouraged an open discussion on the perceptions of the platform. A moderator was then invited to the room to present participants with the key components of the platform and provide tips on its use. At the end of the meeting, the lead facilitator reiterated the purpose of the focus group, summarized what was said, described the next steps, and gave participants the opportunity to bring up discussion points that were not addressed previously but which were of importance to them. These meetings were audio recorded.

During the *HoryzonsCa Exit Interview* (30 minutes), the TAUC-Q and the clinical measures used for the initial interview and the HC-AUSI-Q were completed. The research assistant took field notes including any additional comments that the participant provided related to the website or participation in the project.

#### Feasibility Measures

We also collected data on recruitment rates, appropriateness of eligibility criteria, and the project team’s experience of preparing for and implementing the intervention (based on team meeting notes) mainly to inform the feasibility and design for conducting a larger implementation study in the future.

### Data Management

This study is currently in the data management and analysis phase. The quantitative data from the outcome measures was entered into an Excel file (Microsoft Corporation). All outcome measures at baseline and at the 8 weeks follow-up are either self-reported or interviewer-administered, and those that were completed by the participant were checked by the interviewer for completeness, as sometimes questions are not answered simply because of rushing through, filling in errors, or oversight. Any missing data will be discussed using a team approach to first understand its nature (eg, participant nonresponse, research assistant error in data entry, or participant dropout). We will consider the extent and the type of the missing data (eg, missing completely at random, missing at random, and missing not at random), and then determine the best approach (eg, multiple imputation or regression imputation) to handle the missing data in consultation with a statistician [57]. Once all participants completed the *HoryzonsCa Exit Interview*, website use data was exported to an Excel file.

The qualitative data from the focus group audio recordings will be transcribed and anonymized. The field notes from the *HoryzonsCa Initial Interview and Orientation Meeting* and the *HoryzonsCa Exit Interview* taken by the research assistant will be typed by the research assistant. All qualitative data will be uploaded into the latest version of Atlas.ti software (ATLAS.ti Scientific Software Development GmbH), a coding software package.

### Analysis Plan

Following the convergent mixed methods model, the quantitative and qualitative data will first be analyzed separately and then considered for an integrated analysis of the findings [58]. The quantitative data (including website use data) will first be assessed using descriptive statistics (eg, frequencies). Specifically, to evaluate the acceptability and safety of HoryzonsCa, we will analyze quantitative feedback from the HC-AUSI-Q and website use by calculating proportions (ie, percentage of participants who indicate agree or strongly agree for specific items related to acceptability and safety; percentage of participants with at least 4 log-ins over the 8 weeks follow-up). To assess the potential efficacy of HoryzonsCa, paired samples *t* tests will be conducted on social functioning and clinical measures, and within-group effect sizes (Cohen *d*) will be reported for statistically significant changes between baseline and the 8 weeks follow-up. We will make Bonferroni corrections to reduce the inflation of alpha for multiple comparisons and determine a minimal clinically important difference to detect important changes over time. In addition, exploratory analysis of potential meditators and moderators of treatment effects will be conducted; for example, we will analyze the associations between website use and treatment effects to estimate the moderating role of website use. We will conduct the checks of assumptions prior to conducting analysis, including normality of the data, and will transform the data if needed. Two members of the research team (eg, a postdoctoral fellow and a research assistant) will review data quality (eg, missing data) and determine the best approach (eg, multiple imputation) to handle the missing data in consultation with a statistician and senior members of the research team. Quantitative data analysis will be supported using SPSS (IBM Corp; or R [R Foundation for Statistical Computing]).

Qualitative data (including qualitative feedback from the HC-AUSI-Q and the qualitative data from the interviews and focus groups) will be analyzed and reviewed for themes related to acceptability, perceived benefits, safety, barriers, and facilitators of using HoryzonsCa. Two members of the research team will review all the transcripts, codevelop a coding framework, and conduct a thematic analysis [59] in consultation with the project lead. These will be identified based on their salience with the research objectives and in relation to patterned responses. The coding categories will reflect questions asked during the interview and perspectives that emerged frequently in the data. Qualitative data analysis for the focus groups will be supported using the latest version of Atlas.ti software, a coding software package.

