### Research and Development of Horyzons and Canadian Adaptations

A detailed description of the intervention, its development, and its subsequent adaptation for the Canadian context can be found in our previous published work [30-32]. The first version of Horyzons was developed iteratively over a 30-month period following participatory design principles involving patients, clinical psychologists, computer programmers, health informatics experts, web and graphic designers, and professional writers. It was then pilot-tested on a sample of 20 young adults for its feasibility, acceptability, utility, and safety considerations over 1 month [27]. Results showed that there were no dropouts and incidents (ie, adverse events or inappropriate use) during the pilot, and system use was high, with a total of 275 log-ins. Specifically, 70% of participants used the system for at least 3 weeks, 95% used the social networking features, and 60% completed at least 3 therapy modules. Moreover, all participants found the system easy-to-use, 70% considered it to be a useful long-term treatment option beyond discharge from early interventions services, 100% considered it to be safe, 85% would recommend it to others, and 100% reported moderation to be helpful. With respect to potential clinical improvements, 70% considered the therapy modules to be helpful, and 60% reported that Horyzons significantly increased their social connectedness. Paired samples *t* tests also revealed a significant reduction in depressive symptoms at follow-up (d=0.60; *P*=.02) [27]. The safety strategy pertaining to the intervention study addressed both static (eg, personality trait variables) and dynamic factors (mental health status), and results indicated no clinical or security problems related to the use of Horyzons during the pilot study [27,33]. Additionally, a second version of Horyzons was evaluated in Australia within the context of a 5-year follow-up randomized controlled trial [29], with results recently published. Horyzons has also been piloted in the United States, and preliminary analyses of within-group effect sizes demonstrated the greatest improvements in psychotic symptoms (d=0.65-0.81), followed by depressive symptoms (d=0.14-0.30) and social functioning (d=0.18) [34]. Horyzons has also been adapted for young people at ultra-high risk for psychosis, and preliminary research suggests that it is effective in improving social functioning in this population [35].

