HoryzonsCa will be acceptable to patients. Our conceptualization of acceptability is partially informed by the TAM [37,38], which posits that attitudes toward using a technology influence intention (“acceptance”) to use a technology, which is a direct determinant of behavior [37,38]. The attitude construct is composed of perceived usefulness (an individual’s perception that using an information technology [IT] system will be helpful to them) and perceived ease of use (an individual’s perception that using an IT system will be free of effort) [38]. Patients’ acceptance regarding the use of technologies in health care delivery has been extensively assessed using the TAM model and its derivatives, which highlight the importance of considering factors beyond the individual’s attitudes [41-44]. As such, we also include the concept of adoption in our conceptualization of acceptability, which “is defined as the intention, initial decision, or action to try or employ an innovation or evidence-based practice” [45]. Thus, using this combined understanding of acceptability, in this study, the intervention will be considered acceptable if at least 70% of participants provide positive reports on general experience of the platform, 60% provide positive reports on perceived usefulness (helpfulness), 60% provide positive reports on ease of use, and 60% log onto the site at least 4 times over the 8-week follow-up. These percentages are hypothesized based on the results obtained from the original Horyzons pilot study [27]. We will also determine acceptability through qualitatively assessing perceptions of HoryzonsCa in relation to likes, dislikes, perceived barriers and facilitators to using the platform, and ease of use/experiences of navigating and using its key features (eg, various psychoeducational modules or café) and through exploratory analysis of website use analytics.To assess the safety of the HoryzonsCa platform. *Secondary hypothesis:* HoryzonsCa will be safe, defined as no adverse events, reports, or incidents (eg, hospitalization, suicidal ideation, or disclosure to treatment team regarding harm) related to use of the platform from baseline assessment to 8 weeks follow-up, and at least 70% of participants report that they agree or strongly agree with the perceived safety of the platform and perceived confidentiality of information shared on the platform. We will also determine safety through qualitatively assessing perceptions of the HoryzonsCa platform (eg, experiences, concerns).To assess the potential efficacy of the HoryzonsCa intervention/platform. *Secondary hypotheses:* Participants will show moderate to large improvements (Cohen *d*≥0.5) on measures of social functioning (Social and Occupational Functioning Assessment Scale; Personal and Social Performance Scale) and either improvement of 1 point or no deterioration on the Clinical Global Impression Scale, from baseline to 8 weeks follow-up, as our primary foci for assessing potential efficacy. We will also assess for improvements in social support, self-esteem and perceived strengths, and symptoms. The analysis will help determine pre-post effect sizes on a number of variables conceptually targeted by the platform. These effect sizes will be used in a future clinical trial (eg, randomized controlled trial) for the purpose of statistical power calculation and estimation of sample size.

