### Participants, Sample Size Considerations, Recruitment, and Orientation Process

The target sample is 20 to 25 participants that are patients receiving services from PEPP-Montreal. This sample size was determined by the following factors: feasibility of participant recruitment within a 2- to 3-month time frame, budget related to staffing of moderators, and ensuring adequate number of active users on the platform for the social networking features to function effectively. This sample size has also shown to be sufficient to pilot-test the feasibility and acceptability of Horyzons, as illustrated in the prior pilot study [27] while also acknowledging the limitation of this small sample size for efficacy testing (which is not the main objective of this pilot study). Participant inclusion and exclusion criteria are presented in Textboxes 1 and 2, respectively.

Inclusion criteria.

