## Results

This study was funded by the Brain and Behavior Research Foundation (United States), Quebec Health Research Funding Agency (Canada), and the Canada Research Chairs Program (Canada), and was approved by the Research Ethics Board of the Centre intégré universitaire de santé et de services sociaux de l'Ouest-de-l'Île-de-Montréal on April 11, 2018 (#IUSMD 17-54). The study was registered as a clinical trial at [60] (ISRCTN43182105). Recruitment was initiated on May 10, 2018, and data collection occurred between August 16, 2018, to April 29, 2019. A total of 48 individuals were approached for the study, from which 20 were excluded (17 declined to participate, 1 was not reachable, 1 did not meet inclusion criteria, and 1 met exclusion criteria). The 28 remaining individuals provided informed consent and were invited to complete a baseline assessment, from which 4 did not attend for various reasons (eg, no longer interested, no longer attending clinic, or not feeling well). Among the 24 participants that completed the baseline assessment, 3 dropped out of the study before being given access to the intervention, and 1 was excluded from the intervention soon after team discussion of the baseline assessment due to not meeting inclusion criteria (ie, clinical stability). Upon completion of the baseline assessment and confirmation of eligibility criteria, a final sample of 20 participants were given access to the intervention and none of these were lost at 8 weeks follow-up. Participants were recruited over a 9-month duration (which was 3 times longer than our originally anticipated 3-month timeline), with a recruitment rate of approximately 3 participants per month. A total of 9 participants attended the focus group meetings of approximately 120 minutes each session (4 attended more than once). No adverse events related to the intervention occurred during the live pilot implementation. Further details on the results are expected to be submitted for publication in 2021.

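### Cohen d is to be reported only for statistically significant changes, which conflicts with the aim of supplying effect sizes for planning the next trial and inflates those that appear

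*Protocol article*

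**What the plan says.** The Analysis Plan has paired t tests that "will be conducted on social functioning and clinical measures", and states that within-group Cohen d "will be reported for statistically significant changes between baseline and the 8 weeks follow-up". The next sentence reads: "We will make Bonferroni corrections to reduce the inflation of alpha for multiple comparisons". It gives no nominal alpha, no number of comparisons and no formula for d, and it does not say whether the corrected or the uncorrected alpha decides which effect sizes are shown.

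Objectives and Hypotheses sets two tasks for the same effect sizes. One is a hypothesis about magnitude: "Participants will show moderate to large improvements (Cohen *d*≥0.5) on measures of social functioning". The other is estimation: "The analysis will help determine pre-post effect sizes on a number of variables conceptually targeted by the platform". The article adds there that these values will feed the power and sample-size calculation of a future trial, and the Conclusions repeat this.

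On sample size, "The target sample is 20 to 25 participants that are patients receiving services from PEPP-Montreal"; the Results section records that "a final sample of 20 participants were given access to the intervention and none of these were lost at 8 weeks follow-up". The background section on the development of Horyzons cites within-group effects from a United States pilot, including "followed by depressive symptoms (d=0.14-0.30) and social functioning (d=0.18" for the social functioning domain.

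**The concern.** An estimate shown only when it passes a significance test is a selected estimate. In a study of 20 people the test is passed mainly when chance has pushed the observed change upward, so the values that appear are too large on average and the others are absent. That is the opposite of what a planning exercise needs: the next trial's team needs every estimate, with its uncertainty, and most of all the small ones.

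The rule also fits badly with the efficacy hypothesis. A threshold of d≥0.5 is a statement about size. Whether the observed d reached it should be readable from the report whatever the P value.

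**Working it through.** The article gives no power, alpha or calculated N (20 to 25 rests on feasibility), so there is no figure of its own to reproduce. The check asks what the stated rule does at the achieved sample size.

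**Inputs from the article.** n = 20 with complete follow-up (Results); paired t test, so 19 degrees of freedom (Analysis Plan); hypothesised d of 0.5 on social functioning (Objectives and Hypotheses); 0.18 as the cited social functioning effect from an earlier pilot (background).

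**Assumptions.** Two-sided alpha of 0.05; d = mean change / SD of change; number of tests m in the Bonferroni family taken as 1 (no correction), 2 (the two social functioning scales), 11 (all scales listed under Potential Efficacy) or 12 (the same, counting the two Clinical Global Impression items separately).

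**Step 1: smallest d that can be reported.** Formula: t(1 − 0.05/(2m), 19) / √20, with √20 = 4.472.

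- m = 1: 2.093 / 4.472 = 0.468
- m = 2: 2.433 / 4.472 = 0.544
- m = 11: 3.216 / 4.472 = 0.719
- m = 12: 3.255 / 4.472 = 0.728

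An observed d of exactly 0.50 gives t = 0.50 × 4.472 = 2.236 and P = 0.038. That is significant without correction, but not at 0.05/2 = 0.025.

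**Step 2: how often d is reported as an improvement, and its mean value when it is.** Probabilities come from the noncentral t with noncentrality d√20; conditional means come from simulation.

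| True d | m | Reported | Mean reported d |
|---|---|---|---|
| 0.5 | 1 | 56% | 0.69 |
| 0.5 | 2 | 44% | 0.75 |
| 0.5 | 11–12 | 19–20% | 0.89 |
| 0.18 | 1 | 11.6% | 0.60 |
| 0.18 | 2 | 6.8% | 0.67 |
| 0.18 | 11–12 | 1.6–1.7% | 0.83–0.84 |

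Without selection, the mean observed d would be 0.52 for a true 0.5 and 0.19 for a true 0.18. Nearly all of the excess is therefore due to the filter.

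**Step 3: clash with the d≥0.5 hypothesis.** The probability that a study observes d≥0.5 and does not report it, if the true d is 0.5, is 0 for m = 1 (0.468 is below 0.5), about 7% for m = 2, and 31–32% for m = 11–12.

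**Step 4: sensitivity to the definition of d.** If d is standardised by the raw SD, with equal SDs at both visits, the threshold becomes the Step 1 value × √(2(1 − r)), where r is the pre-post correlation. For m = 2 it is 0.64, 0.54, 0.42 and 0.34 at r = 0.3, 0.5, 0.7 and 0.8; for m = 11 it is 0.85, 0.72, 0.56 and 0.46. It falls below 0.5 once r exceeds about 0.43 (m = 1), 0.58 (m = 2) or 0.76 (m = 11–12). The Step 3 clash can then disappear. The Step 2 selection does not, because the filter still acts on the same t statistic.

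**Step 5: what inflation could do downstream (illustration only).** Suppose a pre-post d were carried over as the between-group d of a two-arm trial, with two-sided alpha 0.05 and 80% power. Then n per arm ≈ 2(1.96 + 0.84)²/d², which gives 63 for d = 0.5, 28 for d = 0.75 and 20 for d = 0.9.

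**The case against.** The best defence has four parts.

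- **The Bonferroni link is inferred.** The reporting rule and the correction stand in adjacent sentences, and nothing says that the corrected alpha decides which d is shown. This stands, and it is why results are given with and without correction. The bias is present in both.
- **A flat contradiction with d≥0.5 is not established.** A reader might infer that any observed d between 0.5 and 0.73 meets the hypothesis yet is hidden. That holds only for about 12 tests with d scaled by the SD of change. With two tests the hidden band is 0.50 to 0.54, with no correction there is none, and a raw-SD d with a high pre-post correlation can remove it. Twelve is also the top of the range: the Clinical Global Impression Scale is judged by a different criterion.
- **The data are not lost.** The team holds every measurement, descriptive statistics are planned, and any reported t gives d = t/√20. So a reader should not conclude that the planning deliverable would be unusable. But the article commits to no effect size or interval for non-significant changes. Selection is also mild for large effects: a true d of 0.81 is reported 93% of the time without correction, at a mean of 0.88 against 0.84 unselected.
- **Efficacy is not the main objective.** The article says so and warns that effects may be missed. This limits the weight of the point. It does not cure the rule, since selection distorts most where power is low.

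**Conclusion.** The point holds. As written, the Analysis Plan ties the reporting of Cohen d to significance, while the objectives and conclusions want effect sizes on a number of variables for planning and judge social functioning by magnitude. At N=20 the rule leaves out a true d of 0.5 in 44% of studies even with no correction, and overstates it at 0.69 on average when it is shown. A Bonferroni filter makes both effects larger. The further claim, that results meeting the d≥0.5 hypothesis can go unreported, is conditional on the corrected alpha governing the filter and on how d is defined.

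The figures rest on a two-sided alpha of 0.05, d as mean change over SD of change, and a family of 1, 2, 11 or 12 tests, none of which the article states. A reader might square the inflation for a true d of 0.18 with 12 tests and conclude that the next trial would be some twenty times too small. The article does not support that: it takes the most extreme case and assumes that a within-group d goes straight into the sample-size formula of a trial whose design is still open. The acceptability and safety objectives are unaffected.

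**What to change.** Replace the reporting rule with a sentence such as: *For every social functioning and clinical measure we will report mean change, SD of change, baseline and follow-up SD, pre-post correlation, and Cohen d (definition stated) with 95% CI, regardless of P value.* State which measures form the Bonferroni family, if a correction is kept, and say that it applies to P values only and does not decide which effect sizes are reported.

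The change needs no new data. Data Management says that the study is still in the data management and analysis phase, so it can be made before results are written up. The cost is a longer table in which many intervals will be wide and some effects small.

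### The Bonferroni correction does not carry over the primary/secondary ranking; if it spans all 11–12 scores, power on each primary functioning scale falls from 44% (37% with the CGI as primary) to about 20%

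*Protocol article*

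**What the plan says.** The Protocol article (Methods, Outcome Measures, Potential Efficacy) ranks the efficacy measures. The "primary clinical measures" are the Social and Occupational Functioning Assessment Scale (SOFAS) and the Personal and Social Performance Scale (PSP). Nine further scales are secondary: the Clinical Global Impression Scale (CGI, two items), perceived social support, self-esteem, strengths knowledge, strengths use, positive symptoms, negative symptoms, the Brief Psychiatric Rating Scale and the Calgary Depression Scale.

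Objectives and Hypotheses sets the efficacy criterion for functioning: "Participants will show moderate to large improvements (Cohen *d*≥0.5) on measures of social functioning". The same sentence adds a CGI criterion and puts all three scales among the primary foci for efficacy. That differs from Potential Efficacy, where the CGI is secondary.

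The Analysis Plan says that "paired samples *t* tests will be conducted on social functioning and clinical measures" and that "within-group effect sizes (Cohen *d*) will be reported for statistically significant changes between baseline and the 8 weeks follow-up". The next sentence says "We will make Bonferroni corrections to reduce the inflation of alpha for multiple comparisons". It gives no alpha, number of comparisons or divisor, and does not separate primary from secondary tests.

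**The concern.** When a plan names two primary measures and nine secondary ones, the primary tests should not lose alpha to the secondary ones unless that is intended. The Analysis Plan names one sentence's worth of pooled tests and then one correction method, with no hierarchy in between. Read that way, SOFAS and PSP are each tested at about 0.004.

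The reporting rule gives this a practical effect. Effect sizes are tied to statistical significance, and Objectives and Hypotheses says they will feed the power calculation of a later trial. The set of tests sharing alpha therefore decides whether the effect size on the main efficacy measures is reported at all.

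**Working it through.** The plan states no power, alpha or divisor, so there is no planned figure to reproduce.

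**Inputs**
- Pairs analysed: n = 20. Results reports that "a final sample of 20 participants were given access to the intervention and none of these were lost at 8 weeks follow-up".
- Effect: d = 0.5, the lower bound in Objectives and Hypotheses. Its standardiser is not stated; assumed here to be the SD of change.
- Alpha: assumed 0.05, two-sided.
- Family size m, counted from Potential Efficacy: 2 primary + 9 secondary = 11 scales, or 12 scores if the two CGI items are counted separately. Alternatives are m = 2 (SOFAS and PSP) and m = 3 (with the CGI).

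**Formulas**
- Per-test level: 0.05/m.
- Power: noncentral t with 19 degrees of freedom and noncentrality 0.5 × √20 = 2.236.
- Smallest significant observed d: critical t divided by √20 (4.472).

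| m | level | critical t | smallest significant d | power at d = 0.5 |
|---|---|---|---|---|
| 1 | 0.05 | 2.093 | 0.47 | 56.5% |
| 2 | 0.025 | 2.433 | 0.54 | 43.9% |
| 3 | 0.0167 | 2.625 | 0.59 | 37.3% |
| 11 | 0.00455 | 3.216 | 0.72 | 20.3% |
| 12 | 0.00417 | 3.255 | 0.73 | 19.4% |

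With 11–12 tests, an observed d on SOFAS or PSP from 0.55 to about 0.71 meets the plan's criterion and would be significant in a two-test family, but is not significant here. Under the reporting rule its effect size would not be shown.

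**Sensitivity to the assumptions (m = 2 against m = 12)**
- One-sided testing: 56.4% against 27.3%.
- d in raw-score SD units, converted by d/√(2(1 − ρ)), where ρ is the pre-post correlation: 31.7% against 12.1% at ρ = 0.3, and 67.5% against 38.7% at ρ = 0.7. At ρ = 0.5 the two definitions of d coincide.
- n = 25, the upper end of the target sample: 55.1% against 28.2%.

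**Choice of procedure.** This was simulated with 20,000 trials per setting, 12 scores, an assumed correlation of 0.3–0.5 between scores and 0.8 between SOFAS and PSP, and a true d of 0.5 on both primaries.

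| procedure | at least one primary significant | both significant |
|---|---|---|
| Bonferroni over 12 | about 27% | 12% |
| Holm over SOFAS and PSP | 55% | 43–44% |
| Holm over 12 | 27–32%, depending on the true secondary effects | not used here |

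As a check, the average of the two Bonferroni figures, (27 + 12)/2 = 19.5%, agrees with the exact 19.4% per scale. The gain comes mainly from restricting the family; changing the procedure alone adds little.

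**The case against.** The strongest objection is that the text does not state a single correction over every paired test. It speaks of corrections in the plural and gives no family. A reader might infer that the plan commits to dividing by 11 or 12, and the document does not say so. If the sponsor meant to correct within the primary pair, power is 44% and the loss does not arise. This stands, so the size of the problem is conditional.

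It can also be said that defining the family belongs in an analysis plan that is not shown. That would answer a complaint about missing detail. But the article does fix a method, and attaches it to a pooled set of tests that ignores its own ranking. Holm gives the same error control as Bonferroni with power never lower, whatever the family.

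A reader might further infer that the correction protects nothing because the secondary measures are exploratory. The document does not support that. It uses that word for website-use analytics and for mediator and moderator analyses, while these scales are called secondary and fall under the efficacy objective. Controlling error across them is a defensible aim: 12 independent tests at 0.05 would carry a familywise error of 1 − 0.95^12 = 46%.

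Finally, the efficacy hypothesis is a threshold on d, not a claim of significance. The sections on sample size and on limitations concede that the study is too small for efficacy testing, and power is below 60% even with no correction. This limits the importance of the point. It does not remove it, because the reporting rule makes significance the condition for showing d.

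**Conclusion.** The concern holds in conditional form. The Analysis Plan applies Bonferroni without carrying over the primary/secondary ranking. If the family is all 11–12 scores, as the text most naturally reads, power on SOFAS or PSP at d = 0.5 and n = 20 is about 20%, against 44% for two tests or 37% for three. The smallest significant observed d moves from 0.54 to 0.72–0.73, further above the plan's criterion of 0.5.

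The result rests on four assumptions: the single family, alpha of 0.05, two-sided testing, and d standardised by the SD of change. Other choices move the levels (12% to 39% at 12 tests for pre-post correlations of 0.3 to 0.7), but the loss from pooling remains large in each case examined.

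The article also disagrees with itself on whether the CGI is a primary efficacy measure, and that decides whether the primary family has two members or three. The point is worth correcting but does not threaten the pilot's main objective, which is acceptability.

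**What to change.** In the Analysis Plan:

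1. Reconcile Objectives and Hypotheses with Potential Efficacy on whether the CGI is a primary efficacy measure.
2. Replace Bonferroni with Holm, and state that the corrected family is the primary functioning measures (plus the CGI, if step 1 makes it primary), with alpha and sidedness given.
3. Report the secondary scores with unadjusted confidence intervals and no significance claim. The rule that ties reporting of d to significance must then be lifted for these scores. Lifting it for the primary measures too is sensible, because even the two-test threshold of 0.54 lies above 0.5.

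The cost is one or two sentences, with no change to data or design. The article describes analysis as still in progress. What is given up is any familywise-controlled claim on the secondary measures.

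If the sponsor wants control over all the scores, Holm should still replace Bonferroni, at no cost in error control or power. The gain is then small: significance on at least one primary measure goes from about 27% to 27–32%.
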